## 4 Statistical methods and sample size

Data analyses will be performed using IBM SPSS Statistics version 20. In addition to the primary analysis, multivariable linear regression will be performed to adjust the primary outcome (24-h VAS score) for potential confounding variables, including age, sex, BMI, ASA physical status, duration of surgery, and tumor size. Exploratory subgroup analyses based on these factors will be conducted if the sample size permits. Normally distributed data will be reported as mean ± standard deviation (mean ± SD), while non-normally distributed data will be presented as median (N) with interquartile range. Categorical data will be shown as percentages (%). Pain scores at different time points will be compared using independent sample *t*-tests, and group comparisons will be analyzed using repeated-measures chi-square analysis. Other metrics will be assessed using χ^2^ tests, *t*-tests, or Mann–Whitney U tests as appropriate. A *p*-value < 0.05 will be considered statistically significant.

Based on prior literature (33), the parameters are set as follows: β = 0.2, α = 0.05, *R* = 1, μ1 = 2.9, μ2 = 3.7, and σ = 1.4. The sample size is calculated using PASS 15.0 statistical software, resulting in 50 effective cases per group. Considering the potential sample loss of 10% and the block size, 112 patients will be enrolled in this study.

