### 2.5 Randomization and blinding

In this study, the method of randomization is block randomization. The block length is eight, and patients will be randomly assigned in a 1:1 ratio to either the liposomal bupivacaine or ropivacaine group. After designing the serial numbers according to the blocks, the numbers will be arranged in ascending order both within and across the blocks. An envelope is encoded for each number. The allocation sequences will be placed in sequentially numbered opaque sealed envelopes. On the day of surgery, a nurse will open the envelope to prepare the solution according to the protocol. The prepared solution will be placed in a light-protected syringe and administered by a neurosurgeon. Participant recruitment will be conducted by an anesthesiologist who will not be involved in data collection and analysis. Upon unblinding, the envelopes will be opened in a strict numerical order. The envelopes will be managed by a certified nurse who will not be involved in any other aspect of the study, beyond managing the envelopes, unblinding the participants, and dispensing medication. Given the single type of surgery and the single-center nature of the study, stratification is deemed impractical. Additionally, the surgical procedure for acoustic neuroma surgery is standardized, with patients usually positioned laterally, and the surgical approach is typically through the sigmoid sinus. A relatively fixed incision area ensures better intervention consistency.

The participants, investigators, and evaluators will be blinded to the study procedure. Owning to the distinct properties of the two drugs, the bupivacaine liposome injection solution appears as a white suspension, whereas the ropivacaine injection solution is a colorless transparent liquid-dark; hence, a light-resistant syringe will be used during dispensing to maintain blinding. This prevents the identification of the agent from the outside. The surgeon is responsible only for scalp injections and will not participate in screening, enrollment, surgical anesthesia, or follow-up. Researchers involved in screening, enrollment, surgical anesthesia, and follow-up, including the patients themselves, will be unaware of the grouping.

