## 3 Outcome measures

### 3.1 Baseline data

Demographic characteristics include body mass index (BMI), age, sex, ASA status, acoustic neuroma size, and comorbidities. Surgical and anesthetic characteristics, including incision length, local anesthetic dosage, duration of surgery and anesthesia, intraoperative analgesic dosages (sufentanil and remifentanil), and hemodynamic parameters will be measured at five time points during the perioperative period.

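### The natural reading is that an unadjusted t-test decides the 24 h VAS comparison; a prespecified baseline-adjusted model would cost only wording and would use precision that may be available

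*Protocol article*

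**What the plan says.** The primary outcome is the 24 h VAS (section 3.2). Section 4 of the protocol article contains three relevant elements.

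- Pain scores at the several time points are compared by independent-samples t-test.
- The trial is sized as an unadjusted comparison of two means, with "β = 0.2, α = 0.05" and "μ1 = 2.9, μ2 = 3.7, and σ = 1.4", "resulting in 50 effective cases per group".
- A covariate model is placed alongside: "In addition to the primary analysis, multivariable linear regression will be performed to adjust the primary outcome". Its covariates are age, sex, BMI, ASA status, duration of surgery and tumour size, and its stated reason is possible confounding.

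No sentence names the primary test outright. The t-test is inferred from the pain-score sentence and from the sample-size inputs.

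Two other sections bear on the point. Section 2.5 says "patients will be randomly assigned in a 1:1 ratio" and explains that stratification will not be used. Section 3.1 shows that the baseline factors are already recorded: "Demographic characteristics include body mass index (BMI), age, sex, ASA status, acoustic neuroma size, and comorbidities". The same section lists duration of surgery separately, among the surgical and anaesthetic characteristics.

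**The concern.** In a randomised trial, baseline factors do not systematically confound the treatment comparison. Adjusting for them helps in two ways: it removes outcome variation that they explain, and it corrects for chance imbalance in them. The main conclusion benefits only if the adjusted model is the analysis that decides. Here the adjusted model is an extra, justified by confounding, while the unadjusted comparison decides.

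Because randomisation is unstratified, covariate adjustment is the remaining way to deal with chance imbalance in prognostic factors. The trial is sized for about 80% power with little to spare, so a few points of power are worth having if they need no extra patients or data.

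**Working it through.** **Inputs.** From section 4: difference 3.7 − 2.9 = 0.8, SD 1.4, α = 0.05, power 0.80, 50 evaluable per group, 10% loss. From section 2.5: 1:1 allocation, and "The block length is eight". Two assumptions are needed. The test is taken as two-sided, which the article does not state; a one-sided test would need 38 per group and does not match. The share of 24 h VAS variance explained by the covariates (R²) is not given, so a range is shown.

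**Step 1: the plan's own figure.**
- Normal approximation: n = 2 × 1.4² × (1.960 + 0.842)² / 0.8² = 48.1, so 49 per group.
- Noncentral t: 49.05, so 50 per group, as stated.
- Loss: 50 / 0.9 = 55.6, so 56 per group and 112 in total, which is 14 blocks of 8.

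The stated sample size reproduces.

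**Step 2: power of the unadjusted t-test at 50 per group.**
- SE = 1.4 × √(2/50) = 0.280.
- Noncentrality = 0.8 / 0.280 = 2.857, with 98 degrees of freedom.
- Power = 80.8%.

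**Step 3: power of a linear model with p baseline covariates.** With N = 100:
- SE = 1.4 × √(1 − R²) × √(2/50) × √(1 + p/(N − p − 3)). The last factor is the expected cost of chance imbalance.
- Degrees of freedom = N − 2 − p.

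For p = 3 (age, sex, tumour size) the imbalance factor is 1 + 3/94 = 1.032, with 95 degrees of freedom.

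| Assumed R² | SE | Noncentrality | Power | Change from 80.8% |
|---|---|---|---|---|
| 0 | 0.284 | 2.813 | 79.5% | −1.3 points |
| 3% | 0.280 | 2.856 | 80.7% | about 0 (break-even) |
| 10% | 0.270 | 2.965 | 83.5% | +2.7 points |
| 20% | 0.254 | 3.145 | 87.5% | +6.7 points |

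**Step 4: the same formula with all six covariates listed in section 4.** The imbalance factor is 1 + 6/91 = 1.066, with 92 degrees of freedom. Power is 78.2% at R² = 0, 82.3% at 10% and 86.5% at 20%, and break-even rises to about 6%. A short covariate list is therefore the better trade at this sample size.

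**Step 5: can the listed model simply be promoted?** No. Duration of surgery is observed after randomisation and after the infiltration, so it is not a baseline factor and does not belong in a primary model of the treatment effect. The other five factors precede randomisation.

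**The case against.** The strongest reply is that nothing here is wrong. An unadjusted primary test with an adjusted supporting analysis is a standard, valid design. The test matches the sample-size calculation, the sample size reproduces, and planned power is met. With no stratification factors, no design feature obliges adjustment. All of this stands, and it limits the point to efficiency.

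The second reply is that the gain is uncertain. The article gives no R². Listing factors as possible confounders does not say that they explain 10% or 20% of pain variation. Table 1 schedules the VAS only from the recovery unit onward, so there is no preoperative pain score to adjust for. This also stands, and it is why the result is given as a range that includes no gain. What the reply does not remove is the asymmetry: with three covariates the worst case is about 1 point of power, against roughly 3 to 7 points at R² of 10% to 20%.

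A reader might also infer that the primary outcome has two p-values, both read at 0.05, and so two chances of a positive result. The article does not support that. By describing the regression as additional to the primary analysis, it ranks the regression below it. A type I error above 5% would need a rule that either result may count, and no such rule is stated. An explicit sentence on what happens if the two analyses disagree is detail that a condensed article may leave to the analysis plan.

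**Conclusion.** The point holds as a cheap improvement. On its natural reading, the plan lets an unadjusted t-test decide and leaves baseline information that will be collected anyway out of the deciding analysis. If age, sex and tumour size are prognostic for 24 h pain, power at 50 per group would rise from 80.8% to 83.5% at R² = 10% or 87.5% at R² = 20%. If they are unrelated to pain, it would fall to 79.5%.

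These figures rest on the plan's own difference and SD, a two-sided test, exactly 50 evaluable patients per group, and an assumed R². Neither the validity of the t-test, nor the sample size, nor control of type I error is in question.

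**What to change.** Before unblinding, state one primary analysis: the between-group difference in 24 h VAS, with its 95% CI, from a linear model with treatment and a few prespecified pre-randomisation covariates, for example age, sex and tumour size. Say that this analysis alone decides superiority. Leave duration of surgery out of that model. Keep the unadjusted t-test as the sensitivity analysis, and give precision, not confounding, as the reason for adjustment.

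The cost is a change of wording. Enrolment stays at 112, and no visit, measurement or form changes. The statistical risk is the loss of about 1 percentage point of power if the chosen covariates turn out to be unrelated to pain.

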## 5 Data collection

The intraoperative anesthesiologists and postoperative follow-up researchers will be blinded to the study design and group allocation. This ensures unbiased data collection of intraoperative vital signs and postoperative pain. This approach minimizes the potential reporting errors. A detailed overview of the collected data is shown in Table 1.

## 6 Data monitoring and management

The study will establish a Data Safety Monitoring Board (DSMB) comprising 10 senior anesthesiologists, surgeons, and statistical experts, each with over 20 years of clinical experience. The DSMB will periodically evaluate the safety of the study, verify the authenticity and integrity of the data, and assess the reliability of implementation procedures. The trial will undergo an annual review by the Ethics Review Committee of Shanghai First People’s Hospital. During this period, the trial will be placed on hold, and participants will not be involved in the review process. Following the review, the trial will either resume or remain suspended based on the audit outcomes. All participants will sign a confidentiality agreement to ensure individual accountability for the accuracy of the data they provide, to maintain data confidentiality, and to protect the privacy of their personal information. All participant information and data will be meticulously recorded in a case report form. Participants who discontinue or deviate from the intervention protocols will not be replaced. Their data will be retained until study completion, except for those who cannot complete the primary outcome assessment. Upon collection and organization, the data will be securely transferred to the principal investigator for storage throughout the duration of the study. Access to the data will be strictly limited to the principal investigator. Other researchers who require access to study data may contact the principal investigator after the completion of the trial to request access, subject to approval and appropriate data-sharing agreements.

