#### 2.4.3 Withdrawal criteria

(1)   Delayed extubation after surgery or admission to the intensive care unit with endotracheal intubation(2)   Need for second operation within the postoperative operation(3)   Poor postoperative cognitive function within 72 h

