### 3.2 Primary outcome

The primary outcome is the 24 h postoperative pain VAS scores.

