### 3.3 Secondary outcome

(1)   Postoperative pain VAS scores: pain VAS scores at 48 h and 72 h postoperatively.(2)   Changes in vital signs: the MAP and HR at five time points: T1 (before anesthesia), T2 (at incision), T3 (during drilling of the skull), T4 (at skin closure), and T5 (at the end of the operation).(3)   Intraoperative and postoperative analgesic use: intraoperative and resuscitation room opioid use, postoperative opioid use on days 1, 2, and 3, and the number and dosage of celecoxib administered will recorded. Data will be statistically converted to morphine doses.(4)   Incidence of PONV: the preoperative Apfel risk score includes four items: female sex, history of PONV or motion sickness, non-smoking status, and history of opioid use. The incidence of PONV in patients with 0, 1, 2, 3, and 4 risk factors is 10, 21, 39, 61, and 78%, respectively. The Alfel risk score ranges from 0 to 4, with higher scores indicating a higher risk. PONV will be assessed using the VAS scale (0–10), where 0 indicates no nausea; 1–4 indicates mild nausea; 5–6 indicates moderate nausea; and 7–10 indicates severe nausea.(5)   Extubation time and PACU stay: time to extubation and duration of stay in the PACU after surgery.(6)   Length of postoperative hospitalization and costs: duration of postoperative hospital stay and associated costs during hospitalization.(7)   Postoperative rehabilitation quality assessment: the 15-item Quality of Recovery Scale will be used to assess postoperative rehabilitation quality. On the third day after surgery or prior to discharge, patients will be asked to complete a 15-question questionnaire (Table 2). Response options range from 0 to 10 points, with 0 indicating poor condition and 10 indicating excellent condition.(8)   Other postoperative complications: incidence and nature of other postoperative complications.

**TABLE 2 T2:** 15-item quality of recovery scale (QoR-15).

Question	Score (0–10)
1. Do you feel that your breathing is comfortable?	
2. Is your appetite good?	
3. Are you able to rest sufficiently and feel energetic as a result?	
4. How is your sleep quality?	
5. Are you able to take care of your personal hygiene independently?	
6. Are you able to have normal conversations with family and friends?	
7. Do you feel supported and cared for by the medical staff?	
8. Are you able to engage in normal work or household activities?	
9. Do you feel comfortable and able to manage your emotions?	

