## 8 Harms

The treatment measures in this study involve the use of local anesthetics for incisional infiltration. There is a risk of local anesthetics entering blood vessels. To mitigate this risk, the syringe is routinely aspirated before the procedure to confirm the absence of blood before proceeding with incision infiltration. However, the concentration of the drugs used in this trial is low, and the dose is small. The physicians performing the procedures are highly skilled, and the administered dose is well below the threshold that can cause local anesthetic toxicity. In the event of accidental symptoms of local anesthetic toxicity or circulatory fluctuations, immediate symptomatic treatment will be administered, and adverse events will be recorded. Adverse events related to study interventions will be treated for free.

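### As worded, Section 6 lets a missing 24 h VAS remove a discontinued or deviating patient's data with no exemption for harms, so complications could go uncounted

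*Protocol article*

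**What the plan says.** Section 6 (Data monitoring and management) first states that "Participants who discontinue or deviate from the intervention protocols will not be replaced". The next sentence refers to the same people: "Their data will be retained until study completion, except for those who cannot complete the primary outcome assessment". Section 3.2 identifies the assessment in question: "The primary outcome is the 24 h postoperative pain VAS scores".

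Section 2.4.3 lists three grounds for withdrawal, all arising after the infiltration: "Delayed extubation after surgery or admission to the intensive care unit with endotracheal intubation"; "Need for second operation within the postoperative operation"; and "Poor postoperative cognitive function within 72 h".

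Other sections call for harms to be collected:
- Table 1 schedules complications and adverse events in the PACU and at 24, 48 and 72 h.
- Section 2.8 says perioperative adverse reactions will be documented.
- Section 3.3, item (8), makes complications a secondary outcome: "Other postoperative complications: incidence and nature of other postoperative complications".
- Section 8, on suspected local anesthetic toxicity, says that "immediate symptomatic treatment will be administered, and adverse events will be recorded".
- Section 6 has all data entered on a case report form and asks the DSMB to evaluate safety periodically.

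**The concern.** An efficacy measurement decides whether a patient's whole record is kept. A missing pain score is a reason to treat the efficacy analysis with care. It is no reason to set aside an adverse event already observed in a patient who received study drug.

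The patients caught by the exception need not be a random subset. The withdrawal grounds are themselves postoperative complications, and each can prevent a patient from scoring pain at 24 h. If their records go, complication and adverse event rates are computed mainly among patients who recovered well enough to give a score. The rates would then tend to be too low, possibly by different amounts in the two arms. Records that have not been kept cannot be recovered at the analysis stage.

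**Working it through.** This is mainly a matter of reading the sections together. The arithmetic only shows the possible scale.

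**1. Whom the exception covers.** In Section 6 the exception attaches to participants who discontinue or deviate. It therefore applies to a patient who (a) is in that group and (b) has no 24 h VAS.

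**2. What it removes.** The sentence speaks of these participants' data as a whole. It does not separate efficacy from safety data.

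**3. How Section 2.4.3 feeds into it.**

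| Withdrawal ground | Can it prevent a 24 h VAS? |
|---|---|
| Delayed extubation or intubated ICU admission | Yes, if it persists to 24 h |
| Second operation | Yes, if near or before 24 h; the stated time window is unclear |
| Poor cognition within 72 h | Yes, if it begins by 24 h; no, if it begins later |

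The overlap is real but partial. A patient withdrawn after giving the 24 h score keeps all data, even on the literal reading.

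**4. Whether another section rescues the harms data.** Table 1 and Sections 2.8, 6 and 8 say that harms are assessed, documented and recorded. None says that the records of patients without a 24 h VAS are kept or counted. Recording an event does not settle whether it is retained and reported.

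**5. The plan's own numbers (Section 4).** Means 2.9 and 3.7 (difference 0.8), SD 1.4, two-sided alpha 0.05 (sidedness assumed), power 0.80.
- The two-sample t-test solution is 49.05, rounded up to 50 per arm, or 100 in all. This reproduces the plan.
- With 10% loss, 100/0.9 = 111.1, so 112 = 14 blocks of 8. This also reproduces.
- Planned loss: 112 − 100 = 12, or 6 per arm if balanced, from 56 enrolled per arm.

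No stated figure is wrong. The 10% is an allowance for loss from any cause, not an estimate of how many patients this clause would affect.

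**6. Illustration.** Assume 6 serious events among 56 patients in one arm. This is not in the documents. The true rate is 6/56 = 10.7%.

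| Patients dropped from the arm | Observed rate |
|---|---|
| None | 6/56 = 10.7% |
| 3, none with an event | 6/53 = 11.3% |
| 3, all with an event | 3/53 = 5.7% |
| 6, all with an event (worst case) | 0/50 = 0% |

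In the worst case the one-sided 95% upper bound is 1 − 0.05^(1/50) = 5.8%, below the true 10.7%. If both arms had 6/56 and only one lost three patients with events, the rule alone would create an apparent difference of 10.7% − 5.7% = 5.0 percentage points.

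**The case against.** The strongest reply is that the sentence is about the analysis set. It follows directly on the statement about replacement and can be read as saying who stays in the outcome dataset. On that reading nothing is deleted, and the commitments elsewhere to document adverse events and complete a case report form stand. A safety population would normally be defined in the full protocol or analysis plan, which is not shown. The trial's stated objective is analgesia, and complications are the last-listed secondary outcome.

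Much of this is fair. The limited reading is plausible, and the absence of a defined safety population in an article is no fault. What remains is that the article states a retention rule, in its data-management section, and does not limit it to efficacy. The limited reading has to be written in.

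Four stronger inferences should be resisted:
- **That these records will be deleted.** This is only one reading of the sentence.
- **That the DSMB could not see the events.** Section 6 does not say when records would leave the dataset or restrict what the board receives. The most one can say is that the board is not assured of seeing them.
- **That every patient without a 24 h VAS is affected.** The clause covers those who discontinue or deviate.
- **That those affected are typically the most severely harmed.** The documents do not say so. A missed assessment or refusal also leaves the score missing. Section 2.4.3 supports only that some will have had complications.

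**Conclusion.** The point holds as a wrongly worded rule. As written, Section 6 can take adverse events and complications of patients withdrawn before 24 h out of outcome (8) and the harms data, contrary to the evident purpose of Table 1 and Sections 2.8 and 8.

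The size cannot be determined from the documents. It depends on how many discontinued or deviating patients lack the 24 h score, how many of those had events, and whether this differs by arm. Under the assumed 6/56, the observed rate could run from about the true 10.7% (or slightly above it, when those dropped had no events) through 5.7% to 0% in a deliberately extreme case. Downward bias requires that events are more common among the dropped patients, which the withdrawal grounds make likely but do not prove.

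The point concerns the harms data only and leaves the sample size unchanged. A reader might go on to infer that no safety conclusion could be drawn from the trial. The documents do not support that, because the limited reading of the clause may be the intended one.

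**What to change.** In Section 6, replace the exception with wording to this effect: a missing 24 h VAS affects only the primary efficacy analysis; all collected data, including adverse events, complications and the reason for discontinuation, are retained for every patient who received the infiltration, whether or not that score is obtained.

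Add that harms are reported by arm in all infiltrated patients, and that the adverse event and complication assessments already scheduled to 72 h in Table 1 continue after withdrawal unless the patient has withdrawn consent.

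The cost is a few sentences and a little more data collection for withdrawn patients, using the existing case report form and time points. No sample size figure changes. Observed complication rates may look slightly less favourable.
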